#### 3.5.3. Sample size

A sample size of 30 participants per group has been determined using G*Power 3.1.3. This calculation was based on a repeated measures ANOVAs (within and between subjects), considering a small to medium effect size of 0.2 [60], as also reported in a two-arm Randomized Control Trial involving chronic stroke participants that also adopted as primary outcome measure the Fugl-Meyer scale [61]. The sample size determination also accounted for 20% attrition, with a significance level (α) set at 0.05 and a desired statistical power of 0.80, as outlined in the literature [62]. Additional, participants will be enlisted in the event of any dropouts.

#### 3.5.4. Recruitment and randomization

Patients considered eligible according to the inclusion criteria will be invited from the IRCCS Istituto delle Scienze Neurologiche di Bologna to participate in the study, explaining in detail the purposes and methods of the study. Before enrolment, informed consent will be obtained from patients. Then, to minimize the risk of bias, the Random Allocation Software 2.0 will be adopted to randomize participants and organize them into blocks of six, that is three participants receiving traditional rehabilitation and three participants receiving the Virtual Reality rehabilitation.

### 3.6. Data management

The participant center will send the case report form (CRF) to the data manager and the study’s principal investigator, and the file will be encrypted. Every patient will receive an alphanumeric identification code that prevents direct identification of the patient’s name. All data collected during the study will be stored and associated with this code. Only the data manager and authorized staff members can associate this code with the patient’s name. Once the data collection is terminated, they will be available from the following DOI: https://doi.org/10.6092/unibo/amsacta/7590.

### 3.7. Statistical analysis

The data analysis follows the Per Protocol approach, that is only participants who have adhered to the study protocol, patients who dropped out of the study are excluded from the analysis. Analysis will be performed through the Statistical Package for Social Sciences (SPSS). Descriptive statistics for both the experimental and control groups will encompass measures such as the mean and standard deviation. The student t-test for independent samples will be used to evaluate the baseline. In case of excessive deviation from normality, a similar non-parametric test (Mann-Whitney) will be used. Changes in motor performance and proprioception between T1 and the subsequent longitudinal evaluations (T2, T3) will be assessed using the repeated measures Analysis of Variance (rmANOVA) with a mixed design 2×3, considering the group as "between subjects" factor and the time point measure as "within subjects" factor. Residual plots will be inspected to verify linearity, normality and homoscedasticity assumptions for all models as well as to identify potential influential outliers. According to the literature, for all inferential analyses the probability of type 1 error is a-priori fixed at alpha α = 0.05 and will include reporting the 95% Confidence Interval for each estimate [62].

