## 2. Objectives and hypothesis

Considering the sensorimotor deficits after a stroke and the relate difficulty to build an internal representation of the own body, plus the significative feature of VR to induce a body illusion, the present protocol aims to investigate the effectiveness of a Virtual Reality rehabilitation program to restore the sensorimotor and proprioceptive abilities of the injured upper limb after a stroke, compared with the treatment as usual (TAU). Moreover, the feature of the exergame of VR would engage the patients and motivate them to pursue the rehabilitation program and overcome the drop-out from the rehabilitation.

### 2.1. Hypothesis 1

VR rehabilitation programs will generally be as effective as TAU in increasing the motor abilities of the injured upper limb after a stroke.

### 2.2. Hypothesis 2

The VR rehabilitation program will be more effective than TAU in the proprioception abilities of the injured upper limb.

### 2.3. Hypothesis 3

The TAU will be the least satisfying rehabilitation program for the patient, with a higher probability of abandonment compared to VR.

### 2.4. Hypothesis 4

The same results will be found across the follow-up assessments (6 and 12 months after intervention).

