## 5. Limitations

Several limitations should be noted in the current clinical trial. Firstly, patient recruitment for stroke cases may prove challenging, given that the stroke unit at Bologna Hospital handles a relatively low number of cases. Secondly, the treatment’s duration—three days a week for four weeks—may pose a limitation, potentially impacting treatment adherence. Thirdly, patients, especially in the initial stages of stroke recovery, may experience clinical complications leading to treatment discontinuation or cessation. Lastly, we anticipate limitations on the technological front, such as technical issues or patients experiencing cybersickness, which could hinder their ability to complete the experimental sessions.

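### The only stated analysis is per protocol with all drop-outs excluded, although the protocol predicts drop-out that differs by arm; the comparison is exposed to selection bias of unknown size and direction, and abandonment is not defined as an outcome

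*Protocol article*

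**What the plan says.** - **Analysis set.** Section 3.7: "The data analysis follows the Per Protocol approach", which it explains as "only participants who have adhered to the study protocol, patients who dropped out of the study are excluded from the analysis". No second analysis set appears in the article.
- **Recruitment after drop-out.** Section 3.5.3 sets 30 per group with an allowance for 20% attrition, and adds: "Additional, participants will be enlisted in the event of any dropouts".
- **Expected drop-out.** Section 2.3 (Hypothesis 3) expects TAU to be the less satisfying programme, "with a higher probability of abandonment compared to VR". Section 2 also hopes that VR will keep patients in rehabilitation. Section 5 foresees clinical complications that end treatment and, for the VR sessions, technical problems or "patients experiencing cybersickness, which could hinder their ability to complete the experimental sessions".
- **Outcomes and tests.** Abandonment is not among the outcomes in sections 3.5.1 and 3.5.2. The tests in section 3.7 cover baseline, motor performance and proprioception. Satisfaction (CSQ-8) is measured once, at T2.
- **Motor hypothesis.** Hypothesis 1 states that "VR rehabilitation programs will generally be as effective as TAU in increasing the motor abilities".

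**The concern.** Adherence and drop-out occur after randomisation. When the analysis set depends on them, the groups compared are those who stayed, not those who were randomised. The groups remain comparable only if staying has nothing to do with outcome, or if selection works in the same way in both arms. This protocol predicts that it will not work in the same way: leaving is expected to differ by arm, and one of the reasons given, clinical complications, is plausibly related to motor recovery.

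At stake are the Fugl-Meyer comparison behind Hypothesis 1, where a shift either way can hide or create a difference, and the superiority claim on proprioception in Hypothesis 2. Hypothesis 3 is affected too. Within the stated set nobody has abandoned treatment, and the T2 satisfaction score would mainly describe those content enough to finish.

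This is a stated rule and not a detail left to another document, so an unseen analysis plan does not remove it.

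**Working it through.** **1. The plan's own figure.** Section 3.5.3 gives 30 per group after 20% attrition, so 30 × 0.8 = 24 completers per group. The 30 cannot be fully reproduced, because neither the within-subject correlation nor the effect tested is stated. For the group-by-time interaction with f = 0.2 and three time points, a correlation of 0.44 gives 48 in total, and 48 / 0.8 = 60. A correlation of 0.5 gives 42, and 42 / 0.8 = 52.5, so 53. The point below does not depend on this.

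**2. Inputs the documents do not give (assumptions).** Drop-out of 30% in TAU and 10% in VR, which averages to the planned 20%. Leavers gain g = 3, 5 or 8 Fugl-Meyer points less than completers. The SD of gain is 8. There is no true difference between arms.

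**3. Bias.** In an arm with drop-out d, the completer mean exceeds the mean of all randomised patients by d × g. The contrast is therefore off by (0.30 − 0.10) × g:
- g = 3: 0.2 × 3 = 0.6 points
- g = 5: 0.2 × 5 = 1.0 points
- g = 8: 0.2 × 8 = 1.6 points

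Under these inputs the shift favours TAU. If VR lost 30% and TAU 10%, it would be the same size in favour of VR. With g = 0, or with equal drop-out and the same mechanism in both arms, it is zero.

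**4. Type I error.** SE = 8 × √(2/n), and the rejection probability is Φ(−1.96 + bias/SE) + Φ(−1.96 − bias/SE).

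| Completers per group | SE | 0.6 points | 1.6 points |
|---|---|---|---|
| 24 | 8 × √(2/24) = 2.31 | 5.8% | 10.7% |
| 30 | 8 × √(2/30) = 2.07 | 6.0% | 12.1% |

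For 1.0 points with 24 per group it is 7.2%. The second row shows what extra recruitment up to 30 completers does: the bias stays and the SE shrinks, so the error rate rises slightly.

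**5. Check by a second method.** Let drop-out remove the lower tail of a latent variable correlated r = 0.5 with the gain. The completer mean then shifts by r × φ(z_d)/(1 − d) in each arm. At 10% versus 30% the contrast is off by 0.15 SD, with type I error 0.081 without further recruitment and 0.090 with it. Splits of 15/25% and 5/35% give 0.08 and 0.23 SD, and 0.06 and 0.12 without further recruitment. With r = 0 the bias is zero, and its sign follows the sign of r.

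**6. Abandonment counted in all randomised patients.** For 10% versus 30% at 30 per arm, the SE under the null is √(2 × 0.2 × 0.8 / 30) = 0.103 and under the alternative √((0.09 + 0.21)/30) = 0.100. Power = Φ((0.20 − 1.96 × 0.103)/0.100) = 0.49. Power of 80% needs 62 per arm. For 15% versus 25%, power is 0.16 and 250 per arm are needed.

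**The case against.** Three stronger readings are tempting, and the documents do not support them.

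- **That the comparison is biased by the trial's own premise.** Hypothesis 3 ties leaving to arm and satisfaction, not to motor gain. Bias also needs leaving to be related to outcome. Section 5 makes this plausible but no figure shows it, and the VR-specific reasons could reverse the imbalance. Section 5 also says only that cybersickness could hinder completion, not that VR patients will leave. What stands is exposure to bias.
- **That Hypothesis 3 cannot be tested at all.** Everyone is randomised and coded, so leavers can be counted by arm, and satisfaction can be compared among those who reach T2. What stands is narrower: the stated analysis set holds no abandoners, and no abandonment outcome or test is defined.
- **That new patients take the places of leavers, or that attrition is counted twice.** Section 3.5.3 says only that "participants will be enlisted in the event of any dropouts". If they are randomised in the usual blocks, this is extra recruitment, and overlap with the 20% allowance is a planning redundancy. The harm comes from the exclusion.

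It is also fair to say that a per-protocol analysis has a recognised place beside an all-randomised one when the claim is that two treatments are equally effective, as in Hypothesis 1. That supports keeping it, not using it alone. Finally, the illustration concerns Fugl-Meyer. Nothing is computed for the Hypothesis 2 measures, and a shift towards TAU would work against that superiority claim.

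**Conclusion.** The point holds in this form: per protocol is the sole stated analysis, the protocol itself expects the excluded patients to differ by arm, and the between-group comparison is therefore exposed to selection bias whose size and direction cannot be known from the documents. Further enlistment restores numbers but not the randomised comparison.

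Under the assumed inputs the bias is 0.6 to 1.6 Fugl-Meyer points, with two-sided type I error of about 6% to 11% at 24 per group and 6% to 12% at 30. These figures rest wholly on an assumed drop-out split, gain gap and SD. At the low end the effect is close to nothing.

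This should be changed before the analysis, and preferably while patients are still being followed, because outcomes never collected from leavers cannot be recovered.

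**What to change.** 1. Make the primary analysis all randomised patients as allocated, with a likelihood-based mixed model (available in SPSS) using every available T1, T2 and T3 value.
2. Keep seeking T2 and T3 assessments from patients who stop sessions.
3. Keep per protocol as a supporting analysis, which is relevant to Hypothesis 1.
4. State that any additional participants are randomised in the usual blocks and do not displace randomised leavers from the analysis.
5. Report abandonment by arm in all randomised patients as a risk difference with 95% CI, and say that power is low (about 0.49 for 10% versus 30% at 30 per arm). Describe CSQ-8 at T2 as applying mainly to completers.

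The cost is protocol wording and some follow-up effort, with the same software and no required increase in sample size. One limit remains: patients with no value after baseline add almost no information on the treatment contrast, and including them rests on a missing-at-random assumption.

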#### 3.5.1. Primary outcome

The primary outcome measures will be the Fugl-Meyer for Upper Limbs [45] employed as a performance-based assessment to characterize motor recovery in research, has demonstrated outstanding reliability. This encompasses internal consistency, inter-rater reliability, intra-rater reliability, and test-retest reliability, particularly in the post-stroke context [59]. The assessment includes 33 items to evaluate upper extremity motor impairment and is scored between 0 and 2 (0 = unable, 1 = partly able, and 2 = fully able to complete movement) with a total score range of 0–66. The assessment will be performed before treatment (T1), after the conclusion of the treatment (T2), and after 6 months as a follow-up (T3).

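### The primary model treats baseline Fugl-Meyer as a time level and not as a covariate, which gives up precision and leaves the primary VR–TAU contrast unnamed

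*Protocol article*

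**What the plan says.** Section 3.5.1 sets the endpoint: "The primary outcome measures will be the Fugl-Meyer for Upper Limbs", measured "before treatment (T1), after the conclusion of the treatment (T2), and after 6 months as a follow-up (T3"). It does not single out T2 or T3.

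Section 3.7 fixes the model. "Changes in motor performance and proprioception between T1 and the subsequent longitudinal evaluations (T2, T3") are to be assessed by "repeated measures Analysis of Variance (rmANOVA) with a mixed design 2×3", with group between subjects and time within. Three levels of time means T1, T2 and T3, so the pre-treatment score is part of the response. No covariate is listed. The only other use of baseline is a comparison of the arms: "The student t-test for independent samples will be used to evaluate the baseline", with Mann-Whitney as the fallback. The section also promises that the analyses "will include reporting the 95% Confidence Interval for each estimate", without saying which estimate carries the primary conclusion.

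**The concern.** Two things are given up.

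- **Precision.** Contrasts against T1 in this model are differences in change. Using the T1 score as a covariate estimates the same treatment difference with smaller variance unless ρ is 1. The trial is small (30 per group), the score is already collected, and section 3.5.4 describes blocks of six with no stratification by baseline score.
- **A stated estimate.** With three time levels the interaction is an omnibus F test on 2 degrees of freedom. It can be significant because of T2, T3 or the path between them, and it has no sign. The hypotheses in section 2 are about VR against TAU, so a reader needs one difference with an interval, chosen in advance.

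The between-arm baseline test adds nothing to either. Among all randomised patients its null hypothesis is true by design, and the test corrects no imbalance.

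**Working it through.** **The plan's own figure.** Section 3.5.3 gives 30 per group from effect size 0.2, α 0.05, power 0.80 and 20% attrition. Reading 0.2 as Cohen's f, the interaction has λ = N·f²·m/(1−ρ), where m is the number of measurements. With m = 3 and ρ = 0.5 this gives N = 42, or 53 after 42/0.8. With ρ = 0.4 it gives N = 50, and 50 × 1.2 = 60. The stated 60 is compatible with an undisclosed ρ and is not shown to be wrong.

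**Variance for the same contrast** (equal SDs, SD = 1, per patient):

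- Change from T1 at one visit: 2(1−ρ).
- Baseline-adjusted: 1−ρ².
- Ratio: (1−ρ²)/[2(1−ρ)] = (1+ρ)/2, which is 0.75, 0.85, 0.90 and 0.95 at ρ = 0.5, 0.7, 0.8 and 0.9.

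For the mean of T2 and T3 under compound symmetry:

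- Unadjusted change: (1+ρ)/2 + 1 − 2ρ = 0.75, 0.45, 0.30, 0.15.
- Baseline-adjusted: (1+ρ)/2 − ρ² = 0.50, 0.36, 0.26, 0.14.

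**Power.** Assumptions: 24 per group (30 less 20%), a difference of 0.4 SD at both T2 and T3, two-sided α 0.05, compound symmetry.

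- Single contrasts: noncentral t with noncentrality 0.4/√(2v/24), where v is the variance above; 46 df unadjusted, 45 df adjusted.
- Planned interaction: noncentral F on 2 and 92 df. The group differences are (0, 0.4, 0.4), whose squared deviations sum to 0.1067, so λ = 12 × 0.1067/(1−ρ) = 1.28/(1−ρ), that is 2.56, 4.27, 6.40 and 12.80.

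| ρ | Planned 2-df interaction | T2 change score | T2-only ANCOVA | T2/T3 mean, change | T2/T3 mean, adjusted |
|---|---|---|---|---|---|
| 0.5 | 0.271 | 0.274 | 0.347 | 0.347 | 0.483 |
| 0.7 | 0.427 | 0.418 | 0.476 | 0.525 | 0.618 |
| 0.8 | 0.599 | 0.573 | 0.618 | 0.697 | 0.758 |
| 0.9 | 0.893 | 0.858 | 0.875 | 0.938 | 0.952 |

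**Reading the table.** From the planned interaction to the adjusted T2/T3 mean, power rises at every ρ shown. The gain has two parts. At ρ = 0.5, naming one contrast moves power from 0.27 to 0.35 and adjustment moves it from 0.35 to 0.48. At ρ = 0.8 the steps are 0.60 to 0.70 and 0.70 to 0.76. T2-only ANCOVA beats the T2 change score throughout, but against the planned interaction it gains little at ρ = 0.8 (0.62 against 0.60) and nothing at 0.9 (0.88 against 0.89).

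**Sensitivity to n.** With 30 analysed per group, λ = 1.6/(1−ρ). Interaction against adjusted mean is then 0.33 and 0.58 at ρ = 0.5, and 0.71 and 0.85 at ρ = 0.8.

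**Sensitivity to effect size.** If f = 0.2 is read as the interaction effect with equal differences at T2 and T3, then 2n × 0.04 × 3 = n·d²/3, so d² = 0.72 and d = 0.849 SD. At that size, with 24 per group and ρ = 0.5, power is already 0.86 for the interaction and 0.92 for T2-only ANCOVA.

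**The case against.** The best defence is that the planned analysis is legitimate. Under randomisation the interaction tests the right null, and a statistician can take T2−T1 and T3−T1 group contrasts, with direction and interval, from the same fitted model. Section 3.7 speaks of changes from T1 and promises intervals, and fuller detail may sit in an analysis plan that is not shown. All of this stands. It limits the point to efficiency and to an unnamed primary contrast. It does not remove the point, because the article itself fixes the model, and that model has baseline as a response level and no covariate.

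Several stronger readings are tempting but not supported:

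- **That the analysis is biased, or yields no between-group estimate at all.** It is valid, and the contrasts can be extracted.
- **That the group main effect, which averages in T1, is the treatment test.** Section 3.7 targets changes from T1 and never says so.
- **That the model is what discards patients seen at T2 but not T3.** A classical rmANOVA does need all three visits, but the exclusion comes mainly from the explicit rule that "patients who dropped out of the study are excluded from the analysis". A different model alone would not bring them back.
- **That 24 per group is the plan's number.** It is an assumption; section 3.5.3 provides for replacing dropouts.
- **That baseline severity is known to vary widely.** No Fugl-Meyer SD is given, and the Motricity Index criteria set both a ceiling and a floor.
- **That adjustment settles Hypothesis 1.** A claim of equal effectiveness also needs a margin.

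The baseline test is a minor matter. The plan does not let it steer any later analysis, and after per-protocol exclusions its null is no longer strictly guaranteed.

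**Conclusion.** The point holds as a loss of efficiency and clarity, not as an error that undermines validity. For any one contrast, adjusting for T1 Fugl-Meyer lowers the variance by 25% at ρ = 0.5 and by 5% at ρ = 0.9. Against the planned interaction, a baseline-adjusted T2/T3 mean raises power from 0.27 to 0.48 (ρ = 0.5), 0.43 to 0.62 (0.7), 0.60 to 0.76 (0.8) and 0.89 to 0.95 (0.9), part of it from concentrating on one contrast.

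These figures rest on assumptions that the document does not supply: ρ, equal SDs, compound symmetry, 24 analysed per group, and an equal 0.4 SD difference at both visits. If the effect were confined to one visit, the averaged contrast would lose its advantage. If the true effect were much larger, power would be high either way. The variance ratio does not depend on the effect size.

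**What to change.** In section 3.7, replace the 2×3 rmANOVA as the primary analysis with a linear mixed model (SPSS MIXED) for the post-treatment Fugl-Meyer scores at T2 and T3. Include group, time, group-by-time and the T1 Fugl-Meyer as covariate. Name one primary contrast in advance, either the T2 difference or the T2/T3 average, and report the adjusted VR–TAU difference with its 95% CI. Use the same model for each secondary scale measured at T1, with its own T1 value. Remove the baseline t-test and Mann-Whitney and describe baseline by arm only. Time since stroke is an optional further covariate.

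The cost is wording and one degree of freedom. The T1 score and time since onset are already collected, and the software is unchanged. The sample-size text in section 3.5.3 is built on rmANOVA and would no longer match the primary model exactly, so a sentence should say so.

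Two related matters need their own changes: keeping patients who have T2 but no T3 requires revising the per-protocol exclusion, and Hypothesis 1 requires a margin.

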## 4. Discussion

The present protocol describes the background and the design of a study that aims to evaluate the effectiveness of a rehabilitation program with VR in improving sensorimotor and proprioception upper limb ability in patients with stroke. The central hypothesis is that the VR rehabilitation program could increase motor facilitation and, as a consequence, improve upper limb control and function compared to the control condition.

The present protocol was developed because motor impairments are the main consequence of stroke, together with the alteration in body representation and the sense of embodiment that prevent limb movements. Much literature has proven VR’s efficacy in motor rehabilitation after a stroke [26, 27]. However, less is known about the modulating role of the body ownership illusion in eliciting rehabilitation. In this line, a recent systematic review [34] demonstrated the significance of body illusion in promoting motor rehabilitation in patients with stroke, both for the upper [22, 63, 64] and lower limbs [23], compared to the control non-embodied condition. The enhanced feature of the embodied VR system, in contrast to conventional rehabilitation programs like the mirror box [58], lies in its ability to evoke motor imagery using computerized images. Additionally, the patient can receive remote feedback on their training, allowing them to ascertain the correctness of their rehabilitation tasks.

In the present protocol, the VR systems, IVR and HB, permit patients to see their real injured arm projected into the virtual environment, which is immersive for the IVR condition and augmented for the HB condition, stimulating the motor cortex [65, 66]. Moreover, thanks to the feature that allows the virtual arm to be adjusted according to the patient’s motor abilities, it is possible to generate an augmented movement even if the patient has minimal ability. Moreover, in contrast to traditional rehabilitation programs, VR treatments are typically well-received by patients due to their immersive environment and increased flexibility in catering to the patient’s clinical characteristics and progress. Additionally, patients have the opportunity to track and record their motor performance [30, 67].

The present protocol provides an integrated approach and requires a multi-professional team, from psychologists to physiotherapists and physiatrist, to plan a well-designed study with the possibility of correlating measures of functional outcomes and neuropsychological assessment.

To conclude, the induction of body ownership illusion in a VR rehabilitation program could be a step forward to traditional therapy that may enhance the upper limb motor recovery after a stroke, thus increasing the patients’ engagement with the treatment.

